### Statistical analysis

SPSS (version 26) will be used for the analysis of this study. Histograms will be used to determine the normality or approximate normality of the data. This will be achieved by combining them with the Shapiro-Wilk test [60]. Descriptive analyses will be performed to examine participant and disease characteristics, as well as data from clinical, circadian rhythm, and neurocognitive functioning assessments. Missing value analyses will be conducted with multiple imputation or expectation maximization methods to handle any missing data.

Spearman correlations will be employed to compare subjective and objectively assessed circadian rhythm patterns. Subjective assessments include MEQ, SPAQ, and PSQI results, while objective assessments will primarily rely on behavioral data.

Longitudinal analyses will involve calculating changes in SAS, SDS, HAMD, HAMA, and YMRS scores, and correlating these difference scores (baseline minus 6-month follow-up, baseline minus 12-month follow-up) with circadian rhythm parameters for each participant using Spearman correlation. Mixed regression models will be used to determine if changes in circadian rhythm significantly predict changes in neurocognitive functioning from baseline to 6-month follow-up and 12-month follow-up [61]. Stepwise adjustment of covariates will be employed to construct several regression models to explore the robustness of the relationship between circadian rhythm and neurocognitive functioning. Adjustments will be made for other factors that may influence these associations, such as disease duration, age, gender, current medication use, education level, and severity of emotional symptoms.

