#### Neurocognitive assessment

The primary outcome will be a comprehensive cognitive composite score. Neurocognitive functioning will be evaluated using the Cambridge Neuropsychological Test Automated Battery (CANTAB), developed by Cambridge Cognition in Cambridge, UK (www.camcog.com) [51]. The tests have undergone validation in studies involving healthy human volunteers as well as various patient groups in the fields of behavioral and psychopharmacological research [52,53]. These tests will be administered on the same day as the actigraph wearing. The selected tests, including Delayed Matching to Sample (DMS), Paired Associates Learning (PAL), Rapid Visual Information Processing (RVP), and Spatial Working Memory (SWM), assess different cognitive domains [54–56]. DMS and PAL evaluate visual memory, RVP measures sustained attention, and SWM reflects executive function. By converting the results of these four tests into Z-scores, the scores of each participant on different cognitive domains can be derived, and a composite cognitive functioning score can be calculated [57,58].

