### Sample size calculation

The sample size for this study was determined based on the primary hypothesis. To calculate the sample size, a review of relevant literature was conducted, and the PASS.15 computer software was used. Due to limited available reports, data from a previous study that evaluated changes in SWM between errors after 1 month of olanzapine treatment in 15 unipolar/bipolar depressive patients was used. In that study, the between errors at baseline and 1-month olanzapine treatment were 34 ± 24 and 21 ± 21, respectively (Mean ± Standard Deviation) [59].

With an assumed power of 0.80 and an alpha level of 0.05, it was determined that a cohort size of 41 at follow-up would achieve 80% power to detect a difference of −13 between the null hypothesis (both baseline and 12-month follow-up means of SWM errors are 34) and the alternative hypothesis (mean of 12-month follow-up is 21). The estimated standard deviations were 21 and 21 at baseline and 12-month follow-up, respectively, using a two-sample *t*-test [54]. Considering a potential dropout rate of 50% and the decision not to replace dropout participants, a total of 81 patients at baseline were deemed necessary. Finally, given the large number of outpatient receptions, we plan to recruit 100 participants.

Therefore, the study aimed to recruit a sample size of 100 patients at baseline to account for potential dropouts and achieve the desired statistical power.

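### Expectation maximization is offered as an equal alternative to multiple imputation; if used to build one completed dataset, it makes standard errors too small and inflates false positives

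*Protocol article*

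**What the plan says.** The Statistical analysis section of the protocol article states: "Missing value analyses will be conducted with multiple imputation or expectation maximization methods to handle any missing data". It gives no rule for choosing between the two methods. It also gives no step that would carry imputation uncertainty into the later models if EM is chosen.

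The same section plans two kinds of longitudinal analysis:
- Spearman correlations of individual change scores on the mood scales (baseline to month 6, baseline to month 12) with circadian parameters.
- Mixed regression models asking whether changes in circadian rhythm predict changes in neurocognitive functioning at 6 and 12 months.

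On the cognitive side, "The primary outcome will be a comprehensive cognitive composite score".

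The Sample size calculation section sets the scale of the missing data: "Considering a potential dropout rate of 50% and the decision not to replace dropout participants, a total of 81 patients at baseline were deemed necessary". It then says "we plan to recruit 100 participants". Under Setting and recruitment, a participant who misses month 6 may still attend month 12, so gaps can also be intermittent.

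**The concern.** The two methods are not equivalent for inference. Multiple imputation with pooling carries the uncertainty about the missing values into the standard error. A single EM-completed file replaces each missing value with one conditional mean and no residual scatter. The software then counts that value as an observation lying exactly on the fitted relation.

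The planned analyses work on each participant's own values, so the most natural way for EM to handle missing data here is to supply filled-in values. With up to half of the month-12 data missing, the result could be confidence intervals that are too narrow. The study could then report that circadian rhythm predicts cognitive change more often than its alpha of 0.05 allows when no such relation exists.

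**Working it through.** **The plan's own figure.** Inputs from the Sample size calculation section: difference 13, SD 21 in both groups, alpha 0.05 (two-sided assumed), power 0.80, two-sample t-test.

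n = 2 × (1.960 + 0.842)² × 21² / 13² = 2 × 7.849 × 441 / 169 = 40.96, so 41. This agrees with the stated 41. Allowing for 50% dropout, 41 / 0.5 = 82, against the stated 81. The planning rate is therefore read correctly. With 100 enrolled, 50% dropout leaves 100 × 0.5 = 50 participants with no month-12 data.

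**Analytic benchmark: one regression with only the outcome missing.** Let a share d of outcomes be filled by conditional means. The filled points add nothing to the residual sum of squares, so the estimated residual variance shrinks by about (1 − d), while n is counted in full. In units of residual SD over predictor SD:
- reported SE ≈ √[(1 − d) / n]
- true SE ≈ √[1 / ((1 − d) n)]
- ratio = 1 − d

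At d = 0.5 and n = 100: √(0.5 / 100) = 0.071 against √(1 / 50) = 0.141, ratio 0.50. Simulation of this case gave a ratio of 0.48 and type I error of 34%. This is a benchmark only, because the article does not plan this model.

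**Three-visit mixed model, closer to the plan.** Simulation assumptions: n = 100, no true effect, normal data missing completely at random, within-person correlation 0.6, random intercept, rhythm and cognition lost together at a missed visit, 50% missing at month 12, 300 replicates per row.

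| Predictor | Missing at month 6 | EM-filled: SE ratio | EM-filled: type I error | Observed visits: SE ratio | Observed visits: type I error |
|---|---|---|---|---|---|
| Change in rhythm | 0% | 0.86 | 10.0% | 1.01 | 3.7% |
| Change in rhythm | 25% | 0.78 | 12.0% | 0.97 | 6.3% |
| Change in rhythm | 50% | 0.68 | 16.7% | 1.01 | 5.3% |
| Baseline rhythm × time | 0% | 0.67 | 16.3% | 1.04 | 4.0% |
| Baseline rhythm × time | 25% | 0.60 | 24.7% | 0.99 | 4.3% |
| Baseline rhythm × time | 50% | 0.55 | 25.7% | 0.98 | 6.7% |

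With 300 replicates, the Monte Carlo error is about √(0.25 × 0.75 / 300) = 2.5 percentage points near 25% and √(0.1 × 0.9 / 300) = 1.7 points near 10%. As a rough check, a ratio r implies type I error of about 2Φ(−1.96 r). That is 28% at r = 0.55 and 9% at r = 0.86, in line with the table.

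**12-month change scores** (n = 100, no true effect, correlation 0.6):
- 50% missing: regression ratio about 0.55 to 0.6; type I error about 24 to 32%, including Spearman on the filled data.
- 20% missing: ratio about 0.84; type I error about 10 to 12%.
- Observed data only: type I error about 5%.

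Varying the correlation from 0 to 0.8, with n of 82 or 100 and 50% missing, widened the regression ratio to 0.51 to 0.70 and type I error to 17 to 31%.

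**The case against.** The strongest reply is that the article does not commit to the harmful use. EM can serve only to estimate means and covariances, and nothing says that one completed file will be made or that dropouts' outcomes will be filled. The sample size section bases power on those remaining at follow-up, and the actigraphy rules exclude non-wear epochs without imputing them, although only at epoch level. This part stands: a reader might infer that the models will run as if all 100 participants were observed, and the text does not say so. The point must therefore be conditional. However, the rank correlations and mixed models need individual values, and the sentence covers all missing data, so a completed file remains the most plausible way to follow the EM option.

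A second reply is that the choice between methods, the number of imputations and the pooling belong in a statistical analysis plan that is not shown. That is fair for the detail, and none of it is held against the article here. The finding concerns a method that the article does name as acceptable.

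A third reply concerns size. A reader might infer that standard errors are halved and that one test in three is a false positive. That follows for a single regression with half the outcomes filled, but not for the planned mixed model, where baseline and some month-6 data are observed. Nor does the article predict that half the cohort will be lost: it calls 50% a potential rate. Describing the study as exploratory, as the Discussion does, lowers the stakes but does not make the standard errors valid.

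**Conclusion.** The concern holds in conditional form. If EM is used to create one completed dataset for the planned analyses, standard errors are too small in every scenario examined:

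- At 50% missing in a three-visit mixed model, they are about 14 to 45% too small (1 − 0.86 to 1 − 0.55), with type I error about 10 to 26%. For change in rhythm as predictor, which is closest to the stated model, the figures are 14 to 32% too small and about 10 to 17%.
- For 12-month change-score analyses at 50% missing, type I error is about 24 to 32%. At 20% missing it is about 10 to 12%, roughly twice nominal.

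The same mixed models fitted to observed visits kept type I error at about 4 to 7%.

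The figures rest on normal data, missingness completely at random, a mostly assumed within-person correlation of 0.6, and a dropout rate that the article gives only as a planning allowance. The article gives neither the correlation nor the missingness pattern, so the exact size is uncertain. The direction is not in doubt: the error favours declaring the hypothesised association.

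**What to change.** In the Statistical analysis section, delete EM as a way to create a completed dataset for inference. Then state three things:

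- The mixed model is fitted by likelihood to the cognitive scores at all observed visits, without filling in outcomes. This is valid under missing at random.
- Multiple imputation, pooled by Rubin's rules, is used only where covariates or actigraphy summaries are missing.
- The Spearman analyses use observed pairs or pooled multiply imputed data.

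The number of imputations and any sensitivity analysis for data missing not at random can be left to the statistical analysis plan.

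The cost is a change of wording, slightly more analysis work, and intervals that are wider but correct. No new data are needed.

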**Figure 1. F0001:**
[figure not shown]
Flow diagram illustrating the procedures for participant enrollment and assessment.

Recruitment will be conducted at the Psychiatric Outpatient Department of The First Affiliated Hospital of Chongqing Medical University in China, which is one of the largest hospitals with an esteemed reputation in southwest China. Recruitment advertisements will be disseminated online, providing contact information for interested patients. Additionally, researchers will proactively contact potential participants based on electronic medical records and expert referrals. Participants will not receive any economic compensation, except for assistance with making outpatient appointments. The recruitment period will span from January 2023 to July 2023. Participants will have the autonomy to withdraw from the study, with reasons and dates recorded. No specific replacement plan is in place for participants who choose to drop out.

The inclusion criteria are as follows: 1) aged 18–45 years old, either female or male; 2) diagnosed with bipolar disorder according to the Diagnostic and Statistical Manual of Mental Disorders-5 (DSM-5), which will be confirmed by researchers using Structured clinical interview for DSM-5, research version (SCID-5-RV) [26,27]; 3) currently in depressive or remitted states, as indicated by a YRMS score < 6; 4) eligible to complete the required examinations; 5) signed written informed consent to participate in this study.

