This study is novel and intriguing due to the following advantages. Firstly, It is the first study protocol to establish the correlation between daily and seasonal circadian rhythms and neurocognitive functioning among BD patients. Secondly, it uses reliable yet less utilized techniques for evaluation accuracies, such as actigraph and CANTAB tests, with a combination of commonly recognized questionnaires for rhythm and mood evaluations. Thirdly, it is a prospective study lasting 12 months that fits in RDoC matrix, which could efficiently fill in the gap of long-term actigraph and cognitive functioning studies. Our study bears the potential to provide stronger evidence than a cross-sectional design and could enlighten similar designs guided by RDoC recommendations [8].

Our study also has some limitations. Initially, we do not explore the melatonin and cortisol levels fluctuations, which is the strongest indication of circadian rhythm [68]. Since we are not able to provide a laboratory condition for such repetitive samples, we are afraid that outpatients could not complete such a complicated measurement outside the hospital. Also, we did not use a sleep diary out of consideration that BD patients lack motivation with no economic compensation. Fortunately, there are some evidences supporting the comparability of cortisol and melatonin tests and sleep diary by actigraph data [69].

Secondly, this study is not a randomized controlled study, and a lot of facts might add bias to this study. This is a single-center study, and most patients will be recruited from our Bipolar Disorder Specialist Clinic, which is less presentative of real-world situations and might decrease the diversity of treatment procedures and medications. Moreover, to strengthen the validity and reliability of data, we minimized the amount of self-rating questionnaires, thus impeding more involvement of useful questionnaires such as the Athens Insomnia Scale, Biological Rhythms Interview of Assessment in Neuropsychiatry, 32-item Hypomania Checklist, Patient Health Questionnaire-9 and General Anxiety Disorder-7 [60,70–73]. Nevertheless, we argue that this is only an exploratory study. More strict study conditions could be set and adapted based on this small-sample study results.

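### Unadjusted Spearman correlations of mood change with circadian parameters can mistake entry mood state for prediction of improvement, in a cohort that mixes depressed and remitted patients

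*Protocol article*

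**What the plan says.** The Statistical analysis section fixes the mood analysis in one sentence. It begins "Longitudinal analyses will involve calculating changes in SAS, SDS, HAMD, HAMA, and YMRS scores" and continues with "correlating these difference scores (baseline minus 6-month follow-up, baseline minus 12-month follow-up) with circadian rhythm parameters for each participant using Spearman correlation". A positive difference therefore means improvement. No baseline score, partial correlation or covariate is attached.

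Covariates come later, with the mixed and stepwise models. These are built "to construct several regression models to explore the robustness of the relationship between circadian rhythm and neurocognitive functioning". The list of adjustment factors that follows ends with "education level, and severity of emotional symptoms". That list refers back to associations in general terms, but it stands directly after the cognitive models, and an ordinary Spearman correlation takes no covariates.

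The inclusion criteria (Setting and recruitment) admit patients "currently in depressive or remitted states, as indicated by a YRMS score < 6". Currently depressed and remitted patients thus enter the same analysis.

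On importance, the Neurocognitive assessment section says "The primary outcome will be a comprehensive cognitive composite score", and the Discussion says "we argue that this is only an exploratory study".

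**The concern.** A patient who enters depressed has room to improve on HAMD, HAMA, SDS and SAS; a patient who enters in remission has little. Baseline minus follow-up on these scales therefore partly records the state in which the patient was recruited. If a rhythm measure is worse during depression, it will correlate with later improvement simply because it marks who was depressed at entry.

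The risk is a directional misreading: disturbed rhythm would look like a predictor of mood improvement. The protocol counts this step among its longitudinal analyses, so a reader could easily take such a result as prognostic.

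**Working it through.** **Inputs.** The plan states no figure for the mood correlations, so there is none to reproduce. From the Sample size calculation section come the planned 100 patients and the 50% dropout allowance, giving 100 × (1 − 0.5) = 50 completers. The 5% level is borrowed from the same section ("With an assumed power of 0.80 and an alpha level of 0.05"). Two inputs are not in the documents and are assumed:

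- ρ, the correlation of the circadian parameter with baseline mood: 0.2 to 0.4, with 0 as a control.
- r, the correlation of baseline with follow-up mood: 0.3 to 0.5, with 0.7 as a milder case.

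**Step 1: induced correlation.** Let B and F be baseline and follow-up mood, each with variance 1, and let x be the baseline circadian parameter. Suppose x carries no information on F once B is known. Then cov(x, B − F) = ρ − ρr = ρ(1 − r), and SD(B − F) = √(2(1 − r)). Hence

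corr(x, B − F) = ρ√((1 − r)/2).

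| ρ | r = 0.3 | r = 0.5 | r = 0.7 |
|---|---|---|---|
| 0 | 0 | 0 | 0 |
| 0.2 | 0.118 | 0.100 | 0.077 |
| 0.3 | 0.177 | 0.150 | 0.116 |
| 0.4 | 0.237 | 0.200 | 0.155 |

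**Step 2: false-positive rate.** Simulation of the same model with normal data, 3,000 runs per cell, n = 50, nominal 5%. Each cell gives raw Spearman, then partial Spearman given baseline:

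| ρ | r = 0.3 | r = 0.5 | r = 0.7 |
|---|---|---|---|
| 0 | 5.4% / 5.2% | 4.9% / 4.6% | 4.5% / 4.7% |
| 0.2 | 13.0% / 5.0% | 10.0% / 4.9% | 8.3% / 4.7% |
| 0.3 | 20.8% / 5.0% | 17.8% / 5.1% | 12.1% / 5.5% |
| 0.4 | 35.7% / 4.7% | 26.9% / 4.7% | 17.6% / 5.6% |

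For ρ of 0.2 to 0.4 and r of 0.3 to 0.5, raw Spearman rejects in 10% to 36% of runs. With 100 patients, which would mean no dropout at all, the same cells give 16% to 62%.

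**Step 3: when adjustment is the wrong model.** Now let x track a stable severity, with baseline and follow-up differing only by measurement error (reliability 0.5 or 0.7, assumed) and no true change. For correlations of x with stable severity of 0.2 to 0.4 and n = 50, raw Spearman rejects in 4.8% to 5.7% of runs. Partialling on baseline rejects in 7% to 18%, with a spurious correlation of −0.06 to −0.15. The sign is opposite to that in Step 1.

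**Step 4: YMRS.** The entry limit restricts the baseline spread. If the follow-up SD is k times the baseline SD, the induced correlation becomes

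ρ(1 − rk)/√(1 + k² − 2rk).

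With ρ = r = 0.3:

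- k = 1: 0.3 × 0.7/√1.4 = 0.18
- k = 2: 0.3 × 0.4/√3.8 = 0.06
- k = 3: 0.3 × 0.1/√8.2 = 0.01

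The artefact fades as k grows, because the difference is then driven mostly by follow-up.

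**The case against.** Five points can be made against the concern.

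- **The mechanism is conditional.** It needs the circadian parameter to correlate with the part of baseline mood that reverts. The documents do not give that correlation, and at zero the raw test is sound. This stands. A reader might infer that entry severity by itself produces a circadian effect; the documents do not support that.
- **Adjustment is not a neutral remedy.** Step 2 uses a model in which baseline adjustment is correct by construction, and Step 3 shows it misleading when the parameter is trait-like. MEQ and SPAQ, which assess chronotype and seasonality and are measured only at baseline (Table 1), may be of that kind. This also stands, and it argues against simply replacing the Spearman analysis.
- **The circadian value is not specified.** The text does not say whether baseline values or changes are correlated with mood change. Actigraphy and PSQI are repeated at each visit, so either is possible for them; the argument here applies to baseline values. MEQ and SPAQ can enter only as baseline values.
- **The mania cap might seem to aggravate the problem.** Step 4 shows the reverse.
- **The analysis is secondary.** Predicting mood change is not among the stated aims, and the study calls itself exploratory. This limits the importance. It does not remove a bias whose direction is predictable. Nor is the point merely detail left to an analysis plan, since the article itself fixes the unadjusted estimator.

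**Conclusion.** The concern holds in a conditional form. For SAS, SDS, HAMD and HAMA, the planned unadjusted correlation can show that a baseline circadian parameter predicts improvement when it only marks mood state at entry. With about 50 completers, the false-positive rate is roughly 10% to 36% under the assumed ρ of 0.2 to 0.4 and r of 0.3 to 0.5. It falls to 8% to 18% at r = 0.7 and is nominal at ρ = 0. These rates rest on assumed correlations, equal variances and normal data.

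A reader might go further and infer that the sign of a true prognostic effect would be reversed. Only the absence of an effect was examined, so that is not shown. For YMRS the argument is weak. The primary cognitive analysis and the sample size are not touched.

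**What to change.** In the Statistical analysis section:

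1. State that the circadian parameters in the mood-change correlations are baseline values.
2. Keep the raw Spearman correlation, and add beside it a regression (or partial Spearman) of follow-up SAS, SDS, HAMD and HAMA on the baseline circadian parameter, adjusted for the baseline value of the same scale and for age, sex and medication.
3. Report the correlation of each circadian parameter with each baseline mood score, so that readers can see whether the condition for the artefact is met.
4. Claim that rhythm predicts mood change only where the raw and adjusted results agree, with both expressed in the direction of improvement. The two artefacts in Steps 1 and 3 have opposite signs, so agreement is a meaningful safeguard.

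The cost is wording and a few extra models; the mood scores are already collected at every visit. The downside is that the adjusted coefficient describes change conditional on the baseline score, and measurement error in that score can bias it for trait-like measures such as MEQ and SPAQ. That is why both analyses should be reported.

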## Abstract

**Introduction:** Bipolar disorder (BD) is a prevalent and disabling mental disorder characterized by disrupted circadian rhythms and impaired neurocognitive features, both of which fall under the major domains of Research Domain Criteria (RDoC). However, there is limited evidence regarding the interaction between circadian rhythms and long-term neurocognitive functioning. Therefore, this longitudinal cohort study protocol aims to explore whether circadian rhythm can predict changes in neurocognitive functioning over time in patients with BD.

**Methods:** This study adopts a longitudinal cohort design, aiming to recruit 100 BD patients in either depressive or remitted states. Participants will undergo evaluations from clinical, circadian rhythm, and neurocognitive perspectives at baseline, 6-month, and 12-month follow-ups, involving questionnaires, actigraphy, and computed neurocognitive tests. We will examine both cross-sectional and longitudinal associations between participants’ circadian rhythm patterns and neurocognitive functioning. Statistical analyses will employ Spearman correlation and mixed regression models.

**Discussion:** We anticipate that circadian rhythms may serve as predictors of neurocognitive functioning changes. The findings of this study could offer supplementary insights into BD pathophysiology, potential treatment targets, and prediction.

**Trial Registration:** This study has been registered with the Chinese Clinical Trial Registry under the registration code ChiCTR2200064922 on 21st October 2022.

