Interestingly, exploring circadian rhythm influence on neurocognitive functioning seems feasible with potential pathophysiological inspirations [13]. Recent studies focusing on Alzheimer’s and other neurodegenerative diseases have speculated on the involvement of seasonal cognitive plasticity and circadian rhythm disruption in neurocognitive functioning changes [14–17]. Additionally, a few pieces of evidence also support such an association with mental disorders [18]. For instance, rats subjected to chronic jet lag simulation demonstrated enhanced depressive behaviors and cognitive deficits [19]. Large-scale UK Biobank data revealed an association between disrupted circadian rhythmicity in mood disorders and cognitive function [20]. Moreover, the ‘desynchronization effect’ resulting from evening chronotypes and circadian disruption might render individuals vulnerable to cognitive and psychiatric challenges [21]. Furthermore, certain molecules are believed to play a role in both circadian rhythm disruption and neurocognitive impairment, mediated through mechanisms like immune-inflammatory activities [22,23].

Regrettably, up to this point, no study has been found that focuses on the long-term clinical correlation between circadian rhythm and neurocognitive functioning in BD patients. Exploring such a correlation holds utmost importance because, if the speculation proves true, 1) it could aid in identifying patients with a worse cognitive prognosis through circadian rhythm evaluation, enabling early intervention when necessary; 2) it may open up new possibilities for treating neurocognitive impairment in BD, for example, from a rhythmic perspective, such as brain synchronization; 3) it would provide stronger evidence supporting the pivotal role of circadian rhythm in BD pathophysiology [24].

Therefore, this study protocol was designed to bridge the current research gaps by investigating the predictability of neurocognitive functioning through circadian rhythm in BD. The objective of this study is to assess whether circadian rhythm could predict the long-term change in neurocognitive functioning among BD patients. It is hypothesized that circadian rhythm could predict the long-term change in neurocognitive functioning.

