#### Circadian rhythm assessment

The circadian rhythm variable consists of two components: subjective questionnaires and objective behavioral data. The questionnaires used include the Morningness Eveningness Questionnaire (MEQ), the Pittsburgh Sleep Quality Index (PSQI), and the Seasonal Pattern Assessment Questionnaire (SPAQ). The MEQ is a 19-item self-rating scale used to evaluate chronotype, with scores indicating evening, intermediate, or morning types [35]. The PSQI is an 18-item self-rating scale that assesses sleep quality and disturbances, and a validated Chinese version will be used [36,37]. The SPAQ is a widely used questionnaire for evaluating seasonal effects on mood and behavior. It includes a general seasonality score (GSS) that can be used to screen for seasonal affective disorder (SAD) [38,39]. Except for the SPAQ, all the aforementioned scales and questionnaires have already been validated or translated into Chinese versions.

On the day of evaluation, participants will be asked to wear a wrist-worn actigraph device (wGT3X-BT, v1.9.2, ActiGraph LLC) for 14 consecutive days and nights. The actigraph’s flashing light will be disabled throughout the monitoring period. The device will continuously record physical activity, sleep/wake information and sedentary time using a sampling frequency of 100 Hz. Participants will be instructed to continuously wear the actigraph except during activities such as showering, swimming, or any activity that would consistently expose the device to water for more than 30 min. Data retrieval and analyses will be performed using the ActiLife software program (version 6.13.4) with 60-second epochs [40]. The collected raw data will be stored and analyzed using publicly available algorithms. Non-wear time will be defined as 60 consecutive minutes of zeros with a 2-minute spike tolerance based on the default Wear Time Validation algorithm provided by Actilife 6.13.4. Any non-wearing epochs will be excluded from the analysis without any data imputation [41,42]. For a day to be deemed valid, it must have a minimum of 20 h of wearing time [42]. A participant will be considered valid if they have a minimum of 7 valid days, including at least 5 weekdays and 2 weekend days [35].

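### The only stated cognition model uses change in circadian rhythm as predictor, apparently over the same interval as the outcome, so as written it does not test whether rhythm predicts later cognitive change

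*Protocol article*

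**What the plan says.** The Introduction sets the aim to "assess whether circadian rhythm could predict the long-term change in neurocognitive functioning among BD patients" and adds: "It is hypothesized that circadian rhythm could predict the long-term change in neurocognitive functioning". The first benefit it lists is "identifying patients with a worse cognitive prognosis through circadian rhythm evaluation, enabling early intervention when necessary". The Anticipated results and Discussion sections repeat the predictive aim. In all of these, rhythm itself is the predictor, it is evaluated first, and cognitive change follows.

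The Statistical analysis section gives one longitudinal analysis of cognition: mixed regression models to "determine if changes in circadian rhythm significantly predict changes in neurocognitive functioning from baseline to 6-month follow-up and 12-month follow-up". Covariates are to be added stepwise: disease duration, age, gender, current medication, education and severity of emotional symptoms. Baseline rhythm is not in that list. The same section correlates circadian parameters, not described as changes, with difference scores, but only for the mood and anxiety scales.

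Table 1 schedules actigraphy and the cognitive tests at baseline, 6 months and 12 months.

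**The concern.** A prognostic claim needs the predictor to be known before the outcome develops. A change in rhythm from baseline to 12 months is known only at 12 months, when the cognitive change is known too. A significant coefficient would then mean that rhythm and cognition moved together. The plan's wording would have it reported as prediction.

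Two consequences follow. First, the result would not separate rhythm acting on cognition from cognition acting on rhythm. Second, a patient whose rhythm is disturbed at baseline and stays disturbed has a rhythm change near zero. If that stable disturbance is what predicts decline, which is the hypothesis as written, the stated model has little chance of finding it.

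**Working it through.** **1. Hypothesis and model side by side.**

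| | Introduction | Statistical analysis |
|---|---|---|
| Predictor | circadian rhythm | change in circadian rhythm |
| Predictor known | at the evaluation, before the outcome | only at the follow-up visit |
| Outcome | long-term cognitive change | cognitive change, 0–6 and 0–12 months |
| Supports | prognosis | association over the period |

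**2. The plan's own figures.** The sample size section gives 41 at follow-up. It reproduces: 2 × [21 × (1.960 + 0.842) / 13]² = 40.96, rounded up to 41. That calculation concerns a mean difference in spatial working memory errors. It says nothing about a rhythm–cognition association, so the plan has no figure of its own on this point.

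**3. Direction.** The correlation between rhythm change and cognitive change is symmetric. The same value arises whichever of the two moved first. No calculation is needed.

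**4. Illustration of the missed baseline effect.**

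From the protocol:
- 100 recruited and 50% dropout allowed for, so 100 × 0.5 = 50 completers
- alpha 0.05, taken as two-sided

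Assumed, not in the protocol:
- true correlation b = 0.4 between baseline rhythm X₀ and later cognitive change ΔY
- standardised rhythm with equal variance at both visits and test-retest correlation ρ of 0.5, 0.7 or 0.9
- one follow-up interval, no covariates

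If X₀ is the only thing related to ΔY, then

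corr(X₁ − X₀, ΔY) = b(ρ − 1) / √(2 − 2ρ) = −b √[(1 − ρ)/2].

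- ρ = 0.5: −0.4 × √0.25 = −0.20
- ρ = 0.7: −0.4 × √0.15 = −0.155
- ρ = 0.9: −0.4 × √0.05 = −0.089

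The sign is opposite to the true effect because a high baseline value tends to be followed by a fall in rhythm.

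Power by Fisher's z is approximately Φ(atanh|r| × √47 − 1.96), plus the small opposite tail. Simulation used 4,000 studies of 50 per setting.

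| Predictor | r | Fisher z | Simulated |
|---|---|---|---|
| Baseline rhythm | 0.40 | 83% | 84% |
| Rhythm change, ρ = 0.5 | −0.20 | 28% | 30% |
| Rhythm change, ρ = 0.7 | −0.155 | 19% | 20% |
| Rhythm change, ρ = 0.9 | −0.089 | 9% | 9% |

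The more stable rhythm is as a trait, the less the change-on-change model sees of it.

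**5. Do the scheduled data allow the right model?** Yes. Baseline actigraphy lasts 14 days and so ends months before the 6- and 12-month cognitive tests. The fault lies in the stated model, not in the data.

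**The case against.** The strongest reply is that one loose sentence in a condensed article is being read as a full specification. The interval in that sentence is attached to the cognitive change. None is given for the rhythm change, so a lagged form is not excluded. This stands as a limit: same-interval change is the natural reading, not the only one. But no lagged or baseline-rhythm predictor is stated, and the point rests on what the sentence names as predictor, not on missing detail.

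The authors also call the study exploratory and say that methods may be adapted to the results. That lowers the stakes but does not turn concurrent association into prediction. It is also a reason to fix the main model before results are seen.

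A reader might infer more than the documents support:

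- *That actigraphy is recorded after the cognitive outcome, so the study cannot test its hypothesis.* The cognitive section says: "These tests will be administered on the same day as the actigraph wearing". The actigraph is worn from the evaluation day for 14 days, so at least 13 of those days follow the test day. The order within the day is not given. Two weeks is small against 6 to 12 months, and the baseline recording still precedes both follow-up tests.
- *That a positive result is equally explained by mood recovery.* The plan adjusts for severity of emotional symptoms, and the mood scales are scheduled at every visit. If severity enters by visit, this confounding is reduced; the protocol does not say whether it does. The adjustment does not settle direction or recover a missed baseline effect.
- *That the baseline-only chronotype and seasonality questionnaires (MEQ, SPAQ) contradict the model.* The Statistical analysis section assigns them to the subjective–objective comparison and does not say that they enter the mixed model.
- *That the cross-sectional analysis is missing.* The Abstract says: "We will examine both cross-sectional and longitudinal associations", and then names Spearman correlation and mixed models. Further detail may sit in a fuller document that is not shown.

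**Conclusion.** The point holds in this form: the one model stated for cognition does not match the objective and hypothesis it is meant to serve. On its natural reading it estimates association between changes over the same visits, and a result from it should not be called prediction.

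The mismatch rests on the wording alone. Its size is illustrative: about 84% power for a baseline-rhythm model against about 9% to 30%, with reversed sign, for change-on-change. Those figures assume 50 completers, a true correlation of 0.4, test-retest correlations of 0.9 to 0.5, and no adjustment for baseline rhythm. Other values would change the percentages. Under the same set-up, the sign reversal remains for any test-retest correlation below 1.

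**What to change.** In the Statistical analysis section, state as the main model a mixed model of the cognitive composite at 0, 6 and 12 months:

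Y = β₀ + β₁T₆ + β₂T₁₂ + β₃X₀ + β₄X₀T₆ + β₅X₀T₁₂ + covariates + participant effect + error,

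where X₀ is the baseline actigraphy rhythm parameter and T₆ and T₁₂ mark the visits. β₅, the difference in 0-to-12-month cognitive change per unit of baseline rhythm, is the test of the hypothesis. Keep the planned covariates and say whether symptom severity enters by visit. A covariate meant to adjust the change, and not only the level, needs its own interaction with time.

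Optionally add a lagged secondary model: 0-to-6-month rhythm change against 6-to-12-month cognitive change. Keep the change-on-change model as secondary and report it as an association. This main model is one reasonable choice; another that places rhythm before the cognitive change would also serve.

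The cost is wording only, since the main model uses measurements already scheduled. The lagged model needs all three visits and so will have fewer participants.
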